**Demographics**		
	Self-report	Self-reported age, gender, ethnic or cultural identity, country of birth, main language, education level, marital status, residential status (duration of homelessness during lifetime and past 6 months), income sources in past 30 days for self and partner (if applicable), including all jobs, Ontario Works, Ontario Disability Support Program, Employment Insurance, Child Benefits, and Child Support
**Health and mental health status**		
	Colorado Symptom Index (CSI)	The CSI (59) measures mental health symptom severity and was specifically designed for and has been widely used among individuals experiencing homelessness and mental health problems. It includes 14 items rated on a five-point scale assessing the presence and frequency of symptoms of mental illness experienced in the past 30 days. Evidence of internal consistency (0.92), test-retest reliability (0.71), and validity is strong and scores are significantly correlated with functioning.
	Global Appraisal of Individual Needs-Short Screener (GAIN-SS)	This screener version of the GAIN (60) has been used extensively in homeless populations with mental health problems to evaluate the severity of substance use problems. It includes a series of questions regarding substance use problems like getting into fights, problems at work, and withdrawal symptoms in recent months. A past month score reflects the frequency with which participants identified past month problems. Other outcomes of interest include the number of days in the past month that participants report problems with substance use; and the amount of money spent on alcohol or drugs in the past month.
	36-Item Short Form Survey (SF-36)	The SF-36 (61, 62) is a widely used measure of generic health status with excellent psychometric properties that has been used successfully in a variety of settings and diagnostic groups, including homeless populations (63). Items span eight domains of health including general health perceptions, vitality, bodily pain, general mental health and limitations in physical, social and usual role activities because of physical or emotional health problems. Scoring yields a Physical Component Summary (PCS) score and a Mental Component Summary (MCS) score.
**Health service use**		
	Self-report	Self-reported number of emergency department visits, hospital admissions, and days in hospital in the past 6 months for pre- and post-randomization.
	ICES administrative data linkage^a^	Number of emergency department visits, hospital admissions, and physician visits in the 12 months pre- and post-randomization.

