### Sample Size

Previous research by our group (48) estimated that for those receiving usual care, the mean number of health-care contacts with program providers per month is 4.6. It was hypothesized that the intervention group will have at least 25% more health-care contacts with program providers per month (mean = 5.8) during the critical transition period. Because the primary outcome represents a count variable, sample sizes for Poisson regression were calculated using the formula provided in Signorini (56). Sample sizes of 67 per group achieve 80% power to detect a rate ratio of 1.25 with a significance level of 0.05 using a two-sided test. However, we expect an attrition rate of 22.0% (44), thus the final sample size per group is inflated by 22%, resulting in a total of 172 study participants. A subsample of study participants (*n* = 22), service providers (*n* = 12), and other key informants (*n* = 6) was estimated a priori as adequate to achieve saturation of qualitative findings and triangulation of data sources.

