### Measures

#### Quantitative Measures

The primary outcome is service engagement, or program attendance, measured as a count of health-care contacts with CATCH service providers per month over the 6-month period (or until discharge from the program). CATCH service providers record program participant attendance in health care appointments and care planning meetings lasting at least 5 min in participant health records. Eligible health-care contacts include in-person and virtual appointments, as well as care planning conversations through email or text. This definition is consistent with the current program practices and ensures only eligible health-care contacts are recorded and reported to the funding agency. Data on program attendance will be captured at study end through chart reviews by a blinded study staff.

Demographic data and other participant characteristics including residential status and income sources were collected by self-report at baseline. Secondary outcome measures of mental and physical health status, health service use, quality of life, and housing are being collected at baseline and 6 months and a measure of perceived therapeutic working alliance is collected at 6 months. Health service use will also be evaluated using data linkage of administrative health records, conducted at ICES, which holds population-based health and health service use information at the patient level for all Ontarians with health insurance.

See Table 1 for a detailed description of all quantitative measures.

**Table 1 T1:** Description of measures.

**Domain**	**Instrument**	**Description of instrument**

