**Working alliance**		
	Working Alliance Inventory-Short Revised (WAI-SR)	This shorter version of the Working Alliance Inventory (74, 75) assesses participant-perceived therapeutic relationship with a case manager. It includes three subscales—task, goal and bond—with items rated on a five-point Likert scale. Scoring yields a single summary score ranging from 12 to 60 with higher scores indicating a stronger therapeutic relationship.

a *Databases accessed and linked by ICES include the National Ambulatory Reporting System, Discharge Abstract Database, Ontario Mental Health Reporting System, and Ontario Health Insurance Plan*.

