##### Secondary Outcome Analysis

For continuous outcomes (i.e., QoLi-20, CSI, SF-36, and EQ-5D VAS), we will define change from baseline to 6-month follow-up as scores at 6 months minus scores at baseline. We will conduct analyses of covariance (ANCOVA) to compare changes from baseline between CATCH-FI and CATCH-UC, adjusting for baseline scores as a covariate.

For count outcomes (i.e., GAIN-SS, number of hospitalizations, number of days hospitalized, and number of emergency department visits) we will model the baseline and 6-month outcomes using generalized estimating equations (GEE) assuming the Poisson distribution or the negative binomial distribution, if over-dispersion is suggested by the data. The models will include the main effects of group (CATCH-FI vs. CATCH-UC) and time (6 months vs. baseline), and the interaction of group by time. A significant interaction will indicate that change from baseline is different between the groups. Rate ratios and 95% confidence intervals will be estimated.

The analysis of administrative data is similar to that of count outcomes, except that the period of consideration will be 12 months instead of 6 months pre and post-randomization.

For analyzing the number of days stably housed in the past 6 months, we will consider GEE with a Poisson or negative binomial distribution. The model will include the main effects of group and time, an interaction between group and time, selected covariates, and an offset represented by the natural log of residence days accounted during the 6 months interval. Rate ratios and 95% confidence intervals will be estimated to compare the rate of days stably housed per person-months.

For the WAI-SR, evaluated at the 6-month follow-up only, total scale, and sub-scales scores will be calculated and compared between the groups using the two-sample *t*-test or the Wilcoxon rank-sum test if extreme outliers are present. The correlation between WAI-SR and other outcomes at 6 months will be explored by estimating the Pearson or Spearman correlation coefficients, overall and by group.

SAS 9.4 will be used for all analyses and all analyses will use the intention-to-treat principle. We will consider multiple imputation to handle missing data. All statistical tests will be two-sided and a *p*-value of 0.05 or less will indicate statistical significance. There are no plans for interim analyses.

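### Days in hospital, a named secondary outcome, is measured only by interview self-report, although inpatient databases are to be linked and will supply admissions

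*Protocol article*

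**What the plan says.** The Secondary Outcome Analysis section of the protocol article lists these count outcomes: "GAIN-SS, number of hospitalizations, number of days hospitalized, and number of emergency department visits". They are to be modelled at baseline and 6 months by GEE with a Poisson or negative binomial distribution.

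Table 1, which the Quantitative Measures section presents as the detailed account of the measures, gives health service use two sources:

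- Interview: "Self-reported number of emergency department visits, hospital admissions, and days in hospital in the past 6 months for pre- and post-randomization".
- ICES linkage: "Number of emergency department visits, hospital admissions, and physician visits in the 12 months pre- and post-randomization".

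Days in hospital appears in the first row and not in the second. The table footnote names the linked sources: "Databases accessed and linked by ICES include the National Ambulatory Reporting System, Discharge Abstract Database, Ontario Mental Health Reporting System, and Ontario Health Insurance Plan". The linkage is planned rather than done ("Health service use will also be evaluated using data linkage of administrative health records, conducted at ICES") and covers Ontarians with health insurance.

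On loss to follow-up, the Sample Size section says "we expect an attrition rate of 22.0" per cent. The Data Collection section allows the follow-up interview from 6 weeks before to 16 weeks after month 6. The analysis section says that multiple imputation will be considered.

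**The concern.** Emergency visits and admissions each have a source that does not depend on finding and interviewing the participant. Days in hospital does not, although the plan already counts admissions from linked inpatient data for the same people. The length-of-stay comparison therefore rests on recall over 6 months, among those who complete the follow-up interview.

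Two things are at stake. One is lost information: a participant who is not interviewed contributes no 6-month value. The other is possible bias, if those not interviewed have a different number of hospital days and are lost at different rates in the two arms. Imputation under the usual missing-at-random assumption would not fully correct loss that depends on the unseen value, although linked admissions and emergency visits could inform the imputation model.

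**Working it through.** **1. Sources of the three hospital-use outcomes in the analysis section**

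| Outcome | Self-report, 6 months | ICES linkage, 12 months |
|---|---|---|
| Emergency department visits | yes | yes |
| Hospital admissions | yes | yes |
| Days in hospital | yes | not listed |

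**2. The plan's own sample size.** Inputs from the Sample Size section are a usual-care rate of 4.6 contacts per month, rate ratio 1.25, two-sided 0.05 and 80% power. The allocation of 1:1 comes from the randomisation section. With one month of exposure and no overdispersion, the Signorini formula gives

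N = (1.96 × √4 + 0.8416 × √(2 + 2/1.25))² / (4.6 × (ln 1.25)²) = 132.9,

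which is 66.4, so 67 per group, as stated. Attrition: 67 / (1 − 0.22) = 85.9, so 86 per group and 172 in total, as stated.

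**3. Expected missing values.** If the 22% is also the rate of missed 6-month interviews, 172 × 0.22 = 37.8. About 38 participants would have no self-reported 6-month days, which leaves about 134.

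**4. What linkage could recover.** Coverage is not stated, so a range is assumed. The standard error relative to 134 participants is √(134/n), other things equal.

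| Assumed coverage | Participants with linked days | Standard error vs 134 |
|---|---|---|
| 100% | 172 | × 0.88 |
| 90% | 155 | × 0.93 |
| 80% | 138 | × 0.99 |

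Linked values alone break even with the interview at 134/172 = 78% coverage.

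**5. Possible bias in the mean (all inputs assumed).** Suppose 10% of participants are in hospital at follow-up with a mean of 40 days, the others have a mean of 8, and overall loss is 22%. The true mean is 0.10 × 40 + 0.90 × 8 = 11.2. If 80% of the inpatients are missed, loss among the others is (0.22 − 0.08)/0.90 = 0.156. The observed mean is then (0.10 × 0.20 × 40 + 0.90 × 0.844 × 8)/0.78 = 8.8, which is 21% too low. If 50% of the inpatients are missed it is 10% too low, and if 22% are missed there is no bias. With 5% to 15% in hospital and 80% of them missed, the shortfall runs from 12% to 28%.

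**6. Possible bias in the comparison (all inputs assumed).** Let interviewed participants average 8 days and lost participants 25 in both arms.

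- Loss of 30% in usual care and 14% in the incentive arm: the true means are 0.70 × 8 + 0.30 × 25 = 13.1 and 0.86 × 8 + 0.14 × 25 = 10.4. The true ratio is 0.79, and the interviewed-only ratio is 8/8 = 1.00.
- Loss of 22% in both arms: both true means are 0.78 × 8 + 0.22 × 25 = 11.7. The true ratio is 1.00, the same as the interviewed-only ratio.

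The distortion in the ratio comes entirely from the assumed 16-point gap in loss between the arms.

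**The case against.** A reader might infer that values will be missing mainly for people who are in hospital at follow-up, or mainly in the usual-care arm. The documents support neither. Nothing says that inpatients cannot be interviewed, and the window up to 16 weeks after month 6 lets many be reached after discharge. Tracing contacts, the follow-up honorarium and the paid contact-update calls are described without distinction by arm. The introduction links poor engagement with return to hospital, and one arm is paid for weekly contact. That makes selective loss plausible but does not establish it.

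The 22% is stated as general attrition used to inflate the sample size for a chart-based primary outcome. Reading it as the missed-interview rate is an assumption.

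Hospital use already has an interview-free measure in linked admissions. The analysis section also says that administrative data are handled much like the count outcomes, a list that includes days. That leaves room for linked days, but it does not say they will be derived, and Table 1 lists the linked variables without them. At best the source is unclear.

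A last objection is to the choice of window. Taking linked days over 12 months as the main value, and filling gaps with 6-month recall, would mix two windows in one outcome and extend past the incentive period. That objection stands, and the change below is framed to avoid it.

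**Conclusion.** The point holds as a gap in the measurement of one secondary outcome. Days hospitalised has self-report as its only listed source, while records that should contain it are to be linked for insured participants. That those records give length of stay is inferred from the names of the databases.

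The size is about 38 of 172 participants without a 6-month value, provided the 22% applies to the interview. Bias in the treatment comparison is a risk and not a finding. It needs loss that is related to hospital use and differs by arm. The figures in steps 5 and 6 show what such loss could do and do not estimate what will happen. The primary outcome, which comes from chart review, is not affected.

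**What to change.** Add total days in hospital to the ICES-linked outcomes in Table 1, derived over two windows:

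- the 6 months before and after randomisation, to match the self-report outcome and the incentive period;
- the 12 months before and after randomisation, alongside the other linked outcomes.

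Name the linked 6-month value as the main source for days hospitalised. Keep self-report as a supportive analysis and use it, over the same 6-month window only, for participants without linkage. State in the Secondary Outcome Analysis section which source and window each analysis uses, and report linkage coverage by arm. Because recruitment is complete, record the change with its date before the linked outcomes are examined.

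The cost is one more derived variable, over two windows, in a linkage already planned. The limits are that participants without Ontario health insurance keep only the self-report, and that the gain shrinks as coverage, which is not stated, falls towards 78%. If the sponsor prefers not to derive linked days, the plan should say why.

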**Quality of life**		
	Quality of Life Index-20 (QoLi-20)	This is a validated shorter version of the Lehman Quality of Life Scale (64) that has been used successfully in the homeless population (65–67). It consists of 20 items across seven subjective scales (reflecting living situation, everyday activities, family, social relationships, finances, safety, and satisfaction with life in general) and four objective scales (reflecting everyday activities, having enough money, family contacts, and contacts with friends).
	5-Level EQ-5D (EQ-5D-5L) and EQ visual analog scale (EQ VAS)	The EQ-5D-5L (68) is the 5-level version of the EQ-5D, a widely used measure of generic health-related quality of life that has been used in populations with mental illness (69). This version asks participants to rate perceived problems on a five-point Likert scale across five dimensions: mobility, self-care, usual activities, pain/discomfort, and anxiety/depression. Scoring is weighted and yields a single utility score between zero and one that describes the user's health state. The EQ VAS asks participants to rate their health on a vertical visual analog scale with opposite ends labeled “The best health you can imagine” and “the worst health you can imagine.” Participants' visual ratings are then assigned to a quantitative value ranging from zero to 100.
**Housing stability**		
	Dartmouth Residential Time-line Follow-Back (RTLFB)	This modified version of the RTLFB (70, 71) has successfully been used in past studies of homeless populations (72, 73). It uses a calendar and prompts to collect detailed information about participants' type of housing and number of days stably housed for specific time periods. A variable representing time spent homeless in the past 6 months in number of days is included as a baseline demographic measure of homelessness. The primary housing outcome of interest from this scale is the number of days stably housed in the past 6 months.
**Working alliance**		
	Working Alliance Inventory-Short Revised (WAI-SR)	This shorter version of the Working Alliance Inventory (74, 75) assesses participant-perceived therapeutic relationship with a case manager. It includes three subscales—task, goal and bond—with items rated on a five-point Likert scale. Scoring yields a single summary score ranging from 12 to 60 with higher scores indicating a stronger therapeutic relationship.

a *Databases accessed and linked by ICES include the National Ambulatory Reporting System, Discharge Abstract Database, Ontario Mental Health Reporting System, and Ontario Health Insurance Plan*.

#### Qualitative Measures

Interviews and focus groups explored the experiences of using financial incentives from both program participant and provider perspectives. Topic guides were developed and iteratively refined by the PI and study staff, with input from people with lived experience of homelessness and mental health challenges. Topics included perceptions of facilitators and barriers to service engagement during care transitions; factors affecting health decision-making in this population; and the perceived risks, barriers, and expected or experienced impact of financial incentives during care transitions. Given ethical concerns and underdeveloped literature on the use of financial incentives, topic guides specifically probed stakeholders to comment on the acceptability of using financial incentives, facilitators of ethical implementation, and potential negative or unintended consequences.

Interviewers' extensive experience with the study population, rigorous interviewer training for this study, and early and ongoing review of transcripts by the PI and study staff helped to ensure consistency across interviews. Investigator triangulation and member checking will help to validate the findings.

### Analyses

#### Quantitative Analyses

Exploratory analyses will calculate descriptive statistics (mean, standard deviation, median, quartiles), construct graphs (histograms, box-plots, scatterplots, spaghetti plots), and estimate correlations between selected participants' characteristics and longitudinal outcomes.

##### Primary Outcome Analysis

Since program duration is customized for each participant, and may last between 1 and 6 months, we will calculate participants' person-months of program participation. This will allow us to estimate the rate ratio comparing the intervention and usual care groups with respect to the number of contacts with CATCH service providers per month. Therefore, for each participant, the total number of months in the program before discharge and the total number of contacts over the number of months in the program will be calculated. A Poisson regression model (PROC GENMOD) with total contacts as the dependent variable, group (CATCH-FI vs. CATCH-UC) as the covariate and an offset equal to the log (number of months spent on the program) will estimate the rate ratio and 95% confidence intervals, and the mean number of contacts per person-months and 95% confidence intervals in each group.

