## Abstract

**Background:** People experiencing homelessness and mental illness have poorer service engagement and health-related outcomes compared to the general population. Financial incentives have been associated with increased service engagement, but evidence of effectiveness is limited. This protocol evaluates the acceptability and impact of financial incentives on service engagement among adults experiencing homelessness and mental illness in Toronto, Canada.

**Methods:** This study protocol uses a pragmatic field trial design and mixed methods (ClinicalTrials.gov Identifier: NCT03770221). Study participants were recruited from a brief multidisciplinary case management program for adults experiencing homelessness and mental illness following hospital discharge, and were randomly assigned to usual care or a financial incentives arm offering $20 for each week they attended meetings with a program provider. The primary outcome of effectiveness is service engagement, measured by the count of participant-provider health-care contacts over the 6-month period post-randomization. Secondary health, health service use, quality of life, and housing outcomes were measured at baseline and at 6-month follow-up. Quantitative data will be analyzed using descriptive statistics and inferential modeling including Poisson regression and generalized estimating equations. A subset of study participants and other key informants participated in interviews, and program staff in focus groups, to explore experiences with and perspectives regarding financial incentives. Qualitative data will be rigorously coded and thematically analyzed.

**Conclusions:** Findings from this study will contribute high quality evidence to an underdeveloped literature base on the effectiveness and acceptability of financial incentives to improve service engagement and health-related outcomes among adults experiencing homelessness and mental illness.

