### Study Participants: Recruitment, Eligibility, and Randomization

The CATCH program receives 450–600 referrals of homeless adults per year, from hospitals or community agencies, prior to or shortly after hospital discharge for a mental health condition. Study participants were recruited among successive new CATCH program participants. Referrals to the study were made by CATCH staff during program intake meetings. Program participants expressing an interest in receiving information about the study were contacted by research staff to confirm interest, eligibility, to obtain informed consent, and to conduct a baseline assessment.

Study participants meet both CATCH program and CATCH-FI study eligibility criteria. Program eligibility criteria include: (1) current homelessness (defined as having no fixed place to stay for at least the past seven nights with little likelihood of finding a place in the upcoming month) or precarious housing (defined as currently occupying a single room in a multi-tenant building or house with shared common areas including bathroom and kitchen or a hotel/motel as a primary residence, and having a history of one or more episodes of absolute homelessness in the past year); (2) service provider-determined unmet mental health needs; (3) service user-determined unmet support needs; and (4) age 18 years or older. Excluded from the program are individuals with recent aggressive behavior requiring a higher intensity of support, or individuals whose illness severity necessitates residential care. To be eligible for the current study, in addition to meeting program eligibility requirements, participants must have been new referrals to CATCH, recently admitted or readmitted to hospital services, and have had at least one contact with the CATCH team.

Participants were randomized following the baseline interview using block randomization (55), which randomizes the participant list into groups 1:1 using blocks of four and six. This approach has the advantage of maintaining balanced group sizes throughout the recruitment process. The nature of the intervention precluded blinding of participants and study staff.

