### Data Collection

Baseline data collection occurred between November 2018 and September 2020; follow-up data collection will be completed in July 2021. All data collection is conducted by trained research assistants from the Survey Research Unit at the Centre for Urban Health Solutions at St. Michael's Hospital. Quantitative surveys lasting 1–2 hwere administered at baseline (up to within 6 weeks of enrollment) and are offered at 6 months post-enrollment (between 6 weeks prior to and up to 16 weeks after that) to all study participants. Survey data are collected using SNAP professional software, and data are held on an internally owned and operated secure sever. All program participants received honoraria paid in-person, by check or email money transfer for each completed interview ($30 for the baseline interview and $60 for the 6-month follow-up interview), in addition to public transportation fare.

Qualitative data collection occurred between April 2019 and December 2020. In-depth, 45–60-min semi-structured interviews were conducted during the study period with program participants and other key informants, and focus groups were conducted with CATCH service providers. Qualitative interview service user participants received an honorarium of $30 and public transportation fare.

This study uses several evidence-based follow-up and study retention strategies for this population (57, 58). To minimize attrition, participants were asked at baseline to provide detailed contact information for themselves and any family, friends, or service providers who could help locate them. To support study retention further, participants were also encouraged to call study staff monthly to update contact information (receiving a $10 honorarium per call). In addition, study staff regularly reach out to participants between interviews to maintain up to date contact records.

A schedule of enrolment, intervention, and assessment is detailed in Figure 1.

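### The primary analysis sets the contact count and the offset over the whole programme stay, while the abstract defines the outcome from randomisation; read literally, the analysis rule pulls the rate ratio toward 1

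*Protocol article*

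**What the plan says.** The protocol article describes the window of the primary outcome in several places, and they do not agree on where it starts.

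- **Abstract:** the outcome is "measured by the count of participant-provider health-care contacts over the 6-month period post-randomization". The start is randomisation.
- **Study Design:** contacts are counted over a 6-month follow-up period. The start is not stated.
- **Quantitative Measures:** the outcome is a "count of health-care contacts with CATCH service providers per month over the 6-month period (or until discharge from the program"). The end is given, the start is not. Table 1 is similar.
- **Primary Outcome Analysis:** because "program duration is customized for each participant, and may last between 1 and 6 months", the analysis computes "the total number of months in the program before discharge and the total number of contacts over the number of months in the program". The model then uses total contacts as the dependent variable and "an offset equal to the log (number of months spent on the program"). Both quantities are tied to the programme stay, and randomisation is not mentioned.

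The order of events is in the section on recruitment, eligibility and randomisation. Programme staff refer people to the study at intake. To be eligible they must "have had at least one contact with the CATCH team". Randomisation follows the baseline interview. Data Collection says surveys were "administered at baseline (up to within 6 weeks of enrollment"), without saying whether enrolment means entry to the programme or to the study.

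**The concern.** Everyone randomised is already a programme client with at least one contact. A rule that counts all contacts and all months in the programme therefore takes in a stretch that the incentive cannot have influenced. In expectation that stretch is the same in both arms, so it enters the numerator and the denominator of both rates equally and moves their ratio toward 1.

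What is at stake is the main effect estimate of the trial. Two analysts, one following the Abstract and the other following Primary Outcome Analysis, would abstract different counts and different person-months from the same charts and report different rate ratios. The authors do anchor other outcomes to randomisation: health service use in Table 1, and the administrative data in Secondary Outcome Analysis, are defined before and after it. The primary model lacks that anchor.

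**Working it through.** **Inputs from the article.** Sample Size: control rate 4.6 contacts per month, target ratio 1.25, 80% power, two-sided 0.05, 67 per group, 172 in total after 22% attrition. Programme stay: 1 to 6 months (Primary Outcome Analysis), 3 to 6 months (Program Description).

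**Assumed, because the article gives no figure.** The gap g from programme intake to randomisation is taken as 0.25 to 1.5 months. The upper value is the 6-week baseline window rounded up (42/30.4 = 1.4 months). The distribution of gap and stay is the same in both arms. The contact rate before randomisation is k times the control rate, with k = 1 unless stated.

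**1. The plan's own figure.** The Poisson-regression sample-size formula with a 1:1 binary covariate is

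N = [1.96·√V0 + 0.8416·√V1]² / (T·4.6·(ln 1.25)²), with V0 = 4 and V1 = 2 + 2/1.25 = 3.6.

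With T = 1 month, N = (3.920 + 1.597)² / (4.6 × 0.04979) = 132.9, or 66.4 per group, rounded up to 67. Then 67/0.78 = 85.9, so 86 per group and 172 in total. The plan's figure is reproduced, and it rests on 1 month of exposure per person.

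**2. Dilution under the literal rule.** A Poisson model with group as its only covariate fits each arm's total contacts divided by its total months. For total stay S,

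observed ratio = (k·g + 1.25·(S − g)) / (k·g + (S − g)).

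With k = 1 this is 1.25 − 0.25·g/S:

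| Stay S | g = 0.25 | g = 0.5 | g = 1 | g = 1.5 |
|---|---|---|---|---|
| 6 months | 1.240 | 1.229 | 1.208 | 1.188 |
| 3 months | 1.229 | 1.208 | 1.167 | 1.125 |
| 2 months | 1.219 | 1.188 | 1.125 | 1.063 |

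If contacts are denser around intake (k = 2), gaps of 0.5, 1 and 1.5 months give 1.212, 1.179 and 1.150 for a 6-month stay, and 1.179, 1.125 and 1.083 for a 3-month stay.

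**3. Negligible gap.** Suppose randomisation follows intake almost at once and only the one required contact is counted, assuming that it qualifies as a health-care contact. With one month after randomisation the ratio is (1 + 5.75)/(1 + 4.6) = 1.21. With three months it is (1 + 17.25)/(1 + 13.8) = 1.23.

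**4. Power.** Solving the formula in step 1 for power at 67 per group, with ratio R and V1 = 2 + 2/R:

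power = Φ{[√(134·T·4.6)·ln R − 1.96·√V0] / √V1}.

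- On the plan's 1-month basis, power is 57% at a ratio of 1.188 and 30% at 1.125. These ratios arise from stays of 2 months or more, so T = 1 does not match them.
- With T equal to the stay and k = 1, a 4.5-month stay with a 1.5-month gap (ratio 1.25 − 0.25 × 1.5/4.5 = 1.167) gives 98.5%. Power is at least that for the 4.5- to 6-month stays examined.
- A 3-month stay with a 1.5-month gap gives 72%, against 93% when only the time after randomisation is analysed.
- A 2-month stay with a 1-month gap gives 54%, against 80%.

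These figures assume pure Poisson variation. The article gives no dispersion figure.

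**The case against.** The strongest reply is that the article nowhere says contacts before randomisation will be counted. The Abstract fixes the start, and Primary Outcome Analysis is there to explain how unequal stays are handled. Its total contacts can be read as the outcome already defined, with the start simply not repeated. Abstraction dates are also the kind of detail that a condensed article leaves to the full document.

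Part of this stands. A reader might infer a deliberate plan to count contacts before randomisation, and the article does not support that. But the section is more than silent. It is the only place where the model's numerator and offset are defined, and it ties both to the programme stay. Charts are reviewed at study end, and someone applying that rule as written would count from intake. The result is a stated rule in conflict with the outcome definition.

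Two further objections stand in full. First, the gap is unknown: the 6-week window may run from study enrolment, in which case it does not measure time since programme entry, and nobody need have waited 6 weeks. Second, a reader might infer that power drops to around a half. That comes from pairing ratios for 4.5- or 6-month stays with a standard error that rests on 1 month of exposure. At 4.5 months the matching Poisson standard error is about 0.037 and power is about 99%. Nor do the extra months add noise in this model, since longer exposure lowers the Poisson standard error.

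**Conclusion.** The point holds as an inconsistency between the Abstract and Primary Outcome Analysis that affects the primary estimate. Read literally, the analysis rule includes contacts and time that the incentive cannot affect, and attenuates the rate ratio.

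The size is conditional. For a true ratio of 1.25, equal contact rates before and after randomisation, and gaps of 0.25 to 1.5 months, the estimate would be about 1.24 to 1.19 for 6-month stays and about 1.23 to 1.13 for 3-month stays. It is trivial if randomisation followed intake within a week or so of a long stay, and material for short stays or long gaps. The gap, the equal rates and the similarity of stays across arms are assumptions.

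Randomisation balances earlier contacts in expectation, so the rule would not produce a false positive finding. Power falls only in some combinations of short stay and long gap, so no general loss can be claimed.

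**What to change.** In Primary Outcome Analysis, state that both the contact count and the person-months in the offset run from the date of randomisation to programme discharge or 6 months, whichever is first. State that the intake contact and any other contact before randomisation are excluded at chart abstraction. Give the same start in Quantitative Measures and Table 1 so that all descriptions match the Abstract.

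The cost is one sentence and a date cut in the chart review. No new data are needed, and the abstractor can be given the randomisation date without the arm, so blinding is kept. Adjusting for the contact rate before randomisation is not needed to cure the problem. Such a rate would be unstable over a gap of a few days and undefined for anyone randomised on the day of intake.
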